### **Intervention**

#### **Control Group**

The participants in the control group will receive usual care, including routine inpatient and discharge education. The hospital's telephone helpline number will also be provided.

#### **Intervention Group**

Participants in the intervention group will receive the 5-week mobile instant messaging-delivered PEI, which was developed by the PI and the research team based on an assessment of caregivers' unmet needs in our previous study. Stress and coping theory was used as the theoretical framework for the development of this intervention. According to this theory, the intervention content will be guided by two coping strategies (problem-based coping and emotion-based coping) based on the caregivers' unmet needs, including worries about the future, informational needs, personal and emotional needs, needs for healthcare access and continuity, and financial needs. To enhance the problem-focused coping strategies, the intervention will provide information to address the caregivers' informational needs, financial needs, and needs for healthcare access and continuity. Emotion-focused strategies function by regulating emotions, modifying the way stress interacts with the environment, or changing the relational meaning of what is happening. Thus, the intervention will mainly educate the caregivers about strategies to cope with their worries about the future and their personal and emotional needs.

Caregivers' informational needs are mainly related to the patient's disease, common treatments, treatment side effects, managing the illness at home, communicating with healthcare professionals, and talking about the illness with the patient. The financial needs mainly involve their need to pay non-medical costs and to receive financial assistance. As we cannot provide direct financial assistance to the caregivers, information about medical insurance and relevant financial assistance programs will be provided. These need-oriented contents will be delivered over five weekly sessions, based on what the caregivers may need each week. For example, in the first week, when the caregivers may need to care for the patients in the hospital, the intervention contents will mainly aim to help the caregivers deal with the medical needs of the patient during their stay in the hospital. Information about the patient's disease, treatments, and treatment side effects; medical insurance and financial assistance programs; how to obtain medical services; and how to communicate with healthcare professionals effectively will be provided in the first week. The contents of each session of the PEI with respect to unmet needs are presented in Table 1.

The whole intervention will be delivered by the PI to ensure intervention consistency. The five sessions of the intervention will be conducted via a mobile instant messaging application, the most popular social media platform in China. This platform allows free instant messages to be sent to individuals or groups through articles and video calls. The first session will be initiated within 1 week

of caregivers recruitment. The following four sessions will be delivered at weekly intervals. At the beginning of each session, a short briefing about the purpose and process of the session will be provided. Towards the end of each session, the intervenor will answer the caregivers' questions and ensure that the caregivers do not have any problems with the content of the current session. At the end of each session, the intervenor will make an appointment with the caregivers for the next session. For sessions one to four, the educational content will be distributed in the form of articles through instant messaging, which are deemed as an effective, sustainable, and feasible strategy for health education. During each session, the PI will send the session-specific articles to the caregivers through instant messaging. The PI will then contact individual participants through video calls via the mobile instant messaging application. During the calls, the PI will use the teach-back strategy to confirm that the participants have read and understood the information provided in the article and will clarify any misunderstandings. The PI will first ask the participants to explain what they have learned in their own words. If there are any misunderstandings, the PI will clarify them. The PI will also discuss the caregivers' problems or concerns with respect to the contents of each session and discuss possible strategies to overcome these problems. The caregivers will be encouraged to express their emotions and concerns throughout the process. In the fifth session, a follow-up call via the mobile instant messaging application will be made to each caregiver to determine whether they have any other unmet needs and if so, they will be able to discuss them.

**Table 1 The mobile instant messaging-delivered psychoeducational intervention for caregivers of adolescent and young adult cancer patients**

| Session          | Coping functions     | Needs                                                        | Content                                                                                                                                                                                                                                                                                                                                                                   | Duration  |
|------------------|----------------------|--------------------------------------------------------------|---------------------------------------------------------------------------------------------------------------------------------------------------------------------------------------------------------------------------------------------------------------------------------------------------------------------------------------------------------------------------|-----------|
| Session 1 | Problem-based coping | Information, financial, and healthcare access and continuity | 
 
• Provide information on cancer, treatments and side effects
 
• Provide information on medical insurance and financial assistance programmes
 
• Teach the caregivers how to obtain healthcare services
 
• Teach the caregivers how to communicate with the healthcare professionals effectively
 
 | 30–45 min |
| Session 2 |                      | Information                                                  | 
 
• Provide information on AYA populations and their fertility issues
 
• Educate the caregivers on how to help manage the patients' illness at home
 
• Educate the caregivers on how to communicate and talk about the illness with the patients
 
                                                          | 30–45 min |
| Session 3 | Emotion-based coping | Personal and emotional                                       | 
 
• Teach the caregivers how to care for themselves
 
• Encourage the caregivers to share their stress and emotions
 
• Teach the caregivers how to manage their stress
 
• Teach the caregivers how to regulate negative emotions
 
                                                                   | 30–45 min |
| Session 4 |                      | Worries about the future                                     | 
 
• Discuss the caregivers' uncertainties or worries
 
• Teach the caregivers how to cope with uncertainty
 
• Encourage optimistic thinking
 
                                                                                                                                                                | 30–45 min |
| Session 5 |                      | Other needs                                                  | 
 
• Discuss the caregivers' other needs
 
                                                                                                                                                                                                                                                                                   | 10–20 min |

## **Outcome Measurements**

### **Sociodemographic and Clinical Characteristics**

We will use a structured data collection form to collect the caregivers' sociodemographic characteristics (i.e. sex, age, educational level, marital status, place of residence, employment, family income, and relationship with the patient) and the patients' sociodemographic characteristics (i.e. sex, age, and type of medical insurance) and clinical characteristics (i.e. type of cancer, age when diagnosed, stage of cancer, and current cancer treatment).

### **Primary Outcomes**

#### **Anxiety**

Anxiety will be measured using the 7-item Generalised Anxiety Disorder Scale (GAD-7), which is a self-reported scale consisting of seven items that measure the respondents' experience of anxiety over the previous 2 weeks. The response options range from "not at all (0)" to "nearly every day (3)". The total score ranges from 0 to 21, with higher scores indicating higher levels of anxiety. The Chinese version of the GAD-7 has demonstrated good internal consistency (Cronbach's alpha = 0.898) and test-retest reliability (intraclass correlation coefficient [ICC] = 0.856). It also has good convergent validity with the Hospital Anxiety and Depression Scale and the Hamilton Depression Scale. The GAD-7 has been widely used to assess caregivers of cancer patients.

#### **Depression**

Depression will be measured using the Patient Health Questionnaire-9 (PHQ-9). This is an instrument used to measure the severity of depression in the general population during the past 2 weeks. A 4-point scale is used to rate the degree of severity from "not at all (0)" to "nearly every day (3)". The total score of the PHQ-9 ranges from 0 to 27, with higher scores indicating higher levels of depression. The simplified Chinese version has shown good internal consistency (Cronbach's alpha = 0.857) and test-retest reliability (ICC = 0.857). It also has good convergent validity with the Hospital Anxiety and Depression Scale and the Hamilton Depression Scale. The scale is widely used to assess the level of depression in caregivers of cancer patients.

### **Secondary Outcomes**

#### **Quality of life**

Caregivers' quality of life will be assessed using the Quality of Life Scale—Family Version (QOL-Scale FAM). The Chinese version has 35 items and four dimensions. Respondents rate each item on a linear scale ranging from 0 to 10. The total score ranges from 0 to 350, with higher scores implying better quality of life. The Chinese version of the QOL-Scale FAM has good reliability and validity, with a Cronbach's  $\alpha$  value of 0.794 for the total questionnaire. It has been used widely to assess the caregivers of patients with various types of cancer.

#### **Coping**

The caregivers' level of coping will be evaluated using the Brief Coping Orientations to Problems Experienced Scale (Brief-COPE). It comprises 28 items that can be categorized into three types of coping strategies: problem-focused strategies, emotion-focused strategies, and dysfunctional coping strategies. Each item is rated on a 4-point Likert scale ranging from "I haven't been doing this at all (1)" to "I've been doing this a lot (4)". No overall score is available for the total scale. The instructions for the tool advise adding the scores for each subscale separately to determine the respondents' usage of each particular coping strategy. A higher score represents greater utilization of a specific coping strategy. The Chinese version of Brief-COPE has sound reliability, and has been widely used to evaluate the coping methods of caregivers of cancer patients.

#### **Unmet needs**

The Support Person's Unmet Needs Survey—Short Form (SPUNS-SF) will be used to measure the caregivers' unmet needs. The Chinese version is a 21-item validated scale used to measure caregivers' unmet needs, including informational needs, worries about the future, financial needs, the need for healthcare access and continuity, and personal and emotional needs. All items are rated with a score of 0 to 4, and a score of 3 or above is classified as a "high-level" unmet need. The scores for all items are summed to calculate the total score, with a higher score representing a higher level of unmet need. The SPUNS-SF has been validated in 1,026 Chinese caregivers of cancer patients and showed good reliability and validity. The internal consistency of the Chinese version of the

SPUNS-SF is high, with a Cronbach's alpha coefficient of 0.94.

### **Data Collection Procedures**

Before baseline data collection, the PI and the research assistants responsible for participant recruitment will assess the unmet needs of the potential participants to determine their eligibility. The eligible participants who consent to participate in the study will be invited to complete questionnaires to perform the baseline assessment. The participants will complete their baseline assessment by filling out paper questionnaires on-site. Follow-up assessments will then be conducted 5 weeks (T1) and 12 weeks (T2) after the baseline assessment. e-Questionnaires will be used for follow-up data collection. The contents of the corresponding questionnaires at each follow-up time point will be input into an e-questionnaire platform (<https://www.wjx.cn/>). The link containing these questionnaires will then be sent to each participant individually through the mobile instant messaging application. The participants will complete the questionnaires independently, given that all questionnaires used in this study are self-reported. To facilitate the participants returning the e-questionnaires on time, the PI will send reminder messages if the questionnaire is not completed on that day. In addition, they will be asked to enter the study ID assigned to them, instead of their names, to protect their privacy. The PI will determine who has completed the questionnaire by identifying their unique study ID. After the participants complete the questionnaires, the PI will thoroughly review the responses for any instances of duplicate records or consecutively consistent answers. If the participants provide consistent answers for ten or more consecutive questions, it will be deemed as straightlining. To ensure the accuracy of the responses in such cases, a research assistant, who is unaware of the intervention allocation, will contact the participants and confirm their responses to these questions.

### **Data Analysis**

All data will be analyzed using SPSS 26.0 (IBM Corp., Armonk, NY, USA). Continuous data will be tested for normality by assessing skewness and kurtosis and by a visual inspection of Q-Q plots. The sociodemographic data and the caregivers' outcomes will be presented using descriptive statistics, as appropriate. The data will be described as means and standard deviations if normally distributed or medians and interquartile ranges if non-normally distributed. Categorical variables will be expressed as numbers (n) and percentages (%). The skewed variables will be appropriately transformed as necessary before testing the intervention effects. A generalized estimating equations (GEE) model will be used to explore the effects of the mobile instant messaging-delivered PEI on the outcomes of interest in this study. The effects of the intervention on the outcome variables will be compared across three time points, namely, T0 (baseline), T1 (5 weeks after baseline), and T2 (12 weeks after baseline) or two-time points (T0 and T1), as appropriate. The control group (assigned as 0) and the baseline (assigned as 0) will be set as the references in the GEE model. The intention-to-treat principle will be followed. The homogeneity between the participants who complete the study and those who drop out will be compared using an independent Student's t-test, Mann-Whitney U test, chi-square test, or Fisher's exact test, as appropriate. If the missing data are deemed to be missing at random, they will be left unaddressed, because GEE models allow data to be missing at random and yield valid results by analyzing the observed data. Otherwise, multiple imputation will be used to impute the missing data.

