### **Sample Size Planning**

The sample size was calculated based on the primary outcomes (anxiety and depression) using G-power (version 3.1.9.7; Heinrich-Heine-Universität Düsseldorf, Düsseldorf, Germany). Considering that no similar study has been conducted for caregivers of AYA cancer patients, the effect sizes of the primary outcomes in previous studies of PEIs for caregivers of adult cancer patients were used to calculate the sample size. The combined effect size for anxiety in previous studies was  $-0.50$ . For a two-tailed  $\alpha$  error of 5%, 80% power, and a test of two independent groups, the required sample size for each group was calculated as 64. An acceptable attrition rate has been shown to be less than 20%. Thus, we assumed an attrition rate of 20% for this study. As a result, the final sample size was calculated as 160 for the two arms. The effect size for depression in previous studies was  $-0.54$ . Based on this effect size, the final sample size was calculated as 138, when using the same parameters as those used for the anxiety outcome. We adopted a larger sample size to guarantee sufficient statistical power. Therefore, the required sample size in this study is 160, with 80 in each group.

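### The trial is sized on a plain two-group test, but the GEE as coded reads most naturally as a difference in change from baseline; adjusting for baseline is more precise at no cost and secures the stated 80% power

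*Protocol*

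**What the plan says.** Protocol, Sample Size Planning, bases the trial on a standardised effect for anxiety of -0.50 ("The combined effect size for anxiety in previous studies was") and, with a two-tailed 5% error, "80% power, and a test of two independent groups, the required sample size for each group was calculated as 64". It then allows for attrition ("Thus, we assumed an attrition rate of 20% for this study") and arrives at 160 in total. For depression the effect is -0.54 ("The effect size for depression in previous studies was") and the total 138; the larger figure is adopted. No correlation between baseline and follow-up enters the calculation.

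Protocol, Data Analysis, uses a GEE that compares the arms over T0, T1 and T2 (or T0 and T1 where only those exist). On coding it says: "The control group (assigned as 0) and the baseline (assigned as 0) will be set as the references in the GEE model". Baseline is thus a level of the outcome. The section does not write out a group-by-time term, the contrast to be tested, whether a group main effect is kept, or a baseline covariate.

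**The concern.** With control and baseline both as reference levels, the ordinary model has group, time and group-by-time terms. The group term is then the difference between arms at baseline, and the group-by-time terms are the differences between arms in change from baseline. That is not the comparison used for sizing. The two have the same variance only when rho is 0.5; below that the change comparison is the weaker, above it the stronger.

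Under Protocol, Design, participants are randomised after baseline data are collected, so the true baseline means of the arms are equal. Estimating a free baseline difference spends information on a quantity known to be zero. At stake are precision on both primary outcomes and whether the stated 80% power belongs to the test that will be run.

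**Working it through.** **Inputs.** From Sample Size Planning: d = 0.50 (anxiety) and 0.54 (depression), two-sided 5%, 80% power, 64 per arm before attrition, 20% attrition. Assumptions not in the protocol: rho (a range is shown), equal SDs over time, and d expressed on the SD of a single time point.

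**The plan's own figures.** A two-sample t-test with the noncentral t gives 64 per arm at d = 0.50 (power 80.1%); 64/0.8 = 80; total 160. At d = 0.54 it gives 55 per arm; 55/0.8 = 68.75, rounded up to 69; total 138. Both reproduce.

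**Variances of the arm difference** (n per arm, SD sigma):
- Single follow-up score, as used for sizing: 2 sigma²/n.
- Difference in change: 2 sigma²/n × 2(1 − rho).
- Baseline-adjusted: 2 sigma²/n × (1 − rho²).
- Adjusted relative to change: (1 − rho²)/[2(1 − rho)] = (1 + rho)/2.

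**Power with 64 completers per arm**, using d/√[2(1 − rho)] for change and d/√(1 − rho²) for adjusted:

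| rho | Change, d = 0.50 | Adjusted, d = 0.50 | Change, d = 0.54 | Variance saved by adjusting |
|---|---|---|---|---|
| 0.2 | 60.2% | 81.7% | 66.9% | 40% |
| 0.3 | 66.0% | 83.7% | 72.6% | 35% |
| 0.4 | 72.7% | 86.5% | 79.0% | 30% |
| 0.5 | 80.1% | 90.0% | 85.8% | 25% |
| 0.6 | 88.1% | 93.9% | 92.4% | 20% |
| 0.7 | 95.2% | 97.6% | 97.5% | 15% |
| 0.8 | 99.3% | 99.7% | 99.8% | 10% |

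**Where the change analysis falls below the stated power:**
- Anxiety, 64 complete cases: 2(1 − rho) = 1, so rho = 0.5.
- Anxiety, if the GEE also uses the baselines of the 16 per arm who drop out: (1 − rho²)/64 + (1 − rho)²/80 = 1/64, which reduces to rho² + 8 rho − 4 = 0, so rho = 0.47.
- Anxiety, no attrition: 2(1 − rho)/80 = 1/64, so rho = 0.375.
- Depression, 64 complete cases: 0.54/√[2(1 − rho)] = 0.50, so rho = 0.42.

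**Total N for 80% power on anxiety with 20% attrition**, change versus adjusted: 224 versus 148 at rho 0.3; 194 versus 136 at 0.4; 160 versus 124 at 0.5; 98 versus 86 at 0.7.

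**Check by simulation.** Exchangeable GEE, 80 per arm, 20% missing both follow-ups, d = 0.50, effect at T2, 400 runs per setting (Monte Carlo standard error up to about 2 points). With a group main effect versus a common baseline mean: 72% versus 84% at rho 0.3; 80% versus 88% at 0.5; 98% versus 99% at 0.7. The 72% exceeds the 66% in the table partly because dropouts' baselines are used: the formula above then gives 69% at rho 0.3, and the rest is within simulation error.

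**The case against.** The strongest reply is that the faulted model is inferred. The protocol fixes reference levels, not terms or contrasts, and a GEE with a common baseline mean is compatible with the quoted sentence. The statistical analysis plan, which is not at hand, may settle this. That stands: the difference-in-change reading is the natural one, not a stated one.

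A reader might go further and infer that the trial is underpowered. The documents do not support that:
- They give no 5- or 12-week correlation. Their only related figures are the test-retest coefficients of 0.856 for the GAD-7 and 0.857 for the PHQ-9 (Protocol, Primary Outcomes). Correlation over 5 to 12 weeks in caregivers during active treatment is probably lower, but nothing places it below 0.5.
- Above 0.5 the change analysis has more power than the plan claims.
- Sample Size Planning does not say on which SD the -0.50 is standardised. If it is the SD of change, there is no shortfall at any rho.

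Nor is the sample size miscalculated. A reader might also infer that chance baseline imbalance biases the result; under randomisation the difference in change is unbiased, so the cost is precision only.

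The objection does not remove the precision argument. Under the natural reading, adjustment has the smaller variance at every rho below 1, although the gain is small when rho is high (5% at 0.9).

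**Conclusion.** This is a free improvement in efficiency, not an error that invalidates the plan. The power statement and the analysis model refer to different comparisons on the natural reading of Data Analysis. A shortfall against 80% requires three things together: the interaction model with a free baseline difference, an effect size on the single-time-point SD, and a rho below about 0.5 for anxiety (0.47 if dropouts' baselines are used) or about 0.42 for depression. None of the three is established by the protocol.

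What holds without knowing rho is that adjusting for baseline, or constraining the baseline means to be equal, beats the difference in change at any rho below 1. It also makes 80% a floor: power is 80.1% at rho 0 and rises from there. At rho exactly 0 the degree of freedom spent on the covariate brings this to about 79.8%, which is immaterial. The floor is for the assumed effect size and 20% attrition.

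**What to change.** In Data Analysis, write out the model and the contrast, in one of two forms:
- T1 and T2 as outcomes, with arm, time, arm-by-time and the baseline score of the same scale as covariate. For unmet needs, which has only T1, this reduces to arm and baseline score.
- T0 kept as an outcome, with a common baseline mean (no group main effect) and a working correlation other than independence, for example unstructured. Under independence the baseline would add nothing to the follow-up contrast.

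In either form, take the arm contrast at follow-up as the treatment effect.

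In Sample Size Planning, state that 80% with 160 participants is then a floor for the assumed effect size and attrition, and say on which SD the effect size is expressed. If the unadjusted interaction is kept, show its power over a range of rho instead.

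The cost is wording only. The baseline scores are already to be collected, and neither the sample size nor the visits change.
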